## Abstract

**Background:**

Osteoarthritis (OA) is a highly debilitating joint disease that causes progressive, irreversible damage to articular cartilage. OA takes a massive toll on society that has grown in recent decades, but no therapy has been shown to halt or reverse the progression of the disease. The critical need for better treatments and increased interest cellular therapies has spawned a new generation of “minimally manipulated” cell treatments. Autologous adipose tissue injections are among the most controversial of these new treatments. Despite a lack of clinical evidence, adipose tissue injections are often marketed as “stem cell” injections with wide-ranging regenerative benefits. The purpose of this study is to estimate the effect size of the treatment by comparing the efficacy of autologous fat to hyaluronic acid (HA). As a secondary aim, we will test for preliminary evidence of efficacy of autologous fat vs. HA.

**Methods:**

This is a prospective, single-center, parallel-group, randomized, controlled trial. Participants (*n* = 54) will receive either a single intra-articular, ultrasound-guided injection of autologous adipose tissue or a single intra-articular, ultrasound-guided injection of HA (1:1 ratio). Outcome data will be obtained at baseline, week-6 and month-6. The Western Ontario and McMaster Universities Osteoarthritis Index (WOMAC) pain domain (WOMAC-A) will be used as the primary outcome measure. Secondary clinical outcome measures include WOMAC (full), clinical anchors (pain, function, and stiffness), and the 29-point Patient-Reported Outcomes Measurement Information System (PROMIS®) profile. We will also take synovial fluid samples and assess sway velocity using a force plate, as well as analyze excess/discard adipose tissue to gain a better understanding of how intra-articular adipose tissue injections influence the biochemical environment of the joint.

**Discussion:**

Given the widespread use of intra-articular fat injections in the United States, it is critical that randomized, controlled human studies evaluating efficacy and biological activity be performed. This study is the first step in addressing this unmet need, but it is not without limitations. The most notable limitations of this study are its small size and lack of blinding, which predisposes the study to both investigator and participant bias.

**Trial registration:**

NCT03242707 // HS-17-00365 // Registration Date (First Posted): August 8, 2018.

**Electronic supplementary material:**

The online version of this article (10.1186/s12891-018-2300-7) contains supplementary material, which is available to authorized users.

## Background

### Introduction

Osteoarthritis (OA) is a debilitating “whole joint disease” that causes progressive, irreversible damage to articular cartilage that results in debilitating joint pain and stiffness [1]. OA places a massive financial burden ln society [2] that has grown in recent decades [3–5]. There are no approved disease modification therapies for OA, and the only non-invasive pharmacologic therapies recommended for OA symptom management are analgesics and non-steroidal anti-inflammatory drugs (NSAIDs) [6, 7]. Intra-articular therapies, including corticosteroids and hyaluronic acid (HA) are frequently used to treat knee OA, but both treatments have limitations. The American Academy of Orthopaedic Surgeons (AAOS) determined that there was inconclusive evidence to support the use of intra-articular corticosteroids of OA [8] and several recent studies have suggested that corticosteroids may have detrimental catabolic effects on cartilage [9–11]. While generally assumed to be safe, the AAOS concluded that the apparent effectiveness of HA compared to saline placebo is clinically negligible, and strongly recommended against its use [12]. The recommendation has been met by push back [12, 13], and meta-analysis published since have both confirmed [14] and contradicted [15] the appropriateness of the AAOS recommendation. Nevertheless, even if assumed to be effective, HA provides (at best) modest, short-term, symptomatic relief compared to placebo control.

OA is frequently referred to as a “wear and tear” disease. However, OA pathophysiology is multifactorial, and complex interactions between genetic, metabolic, biochemical, and biomechanical factors are also likely to play an important role in the progression of the disease [16, 17]. In recent years, studies have suggested that inflammatory mechanisms contribute to OA pathogenesis, particularly synovitis, which has been correlated with the structural progression of OA, cartilage degeneration and osteophyte formation [18]. Indeed, an emerging body of evidence indicates that OA is a whole-organ disease that involves the production of cytokines by a variety of different tissues [1, 19] and a number of cytokines have been implicated in OA pathogenesis [20–24].

There is considerable interest in exploiting the anti-inflammatory activities of cellular treatments to treat OA [25]; however, adipose tissue-derived cell therapies require enzymatic processing and isolation techniques that may impact safety and efficacy [26]. These concerns have prompted the United States Food and Drug Administration (US FDA) to regulate autologous cell therapies that have been cultured and/or enzymatically processed as drugs. The promise of cellular therapies, particularly those containing so called mesenchymal “stem” or stromal cells (collectively referred to as MSCs), combined with regulatory barriers and the critical need for new therapies, has spawned a new generation of “minimally manipulated” cell treatments for OA. Among these new “minimally manipulated” cell treatments are autologous adipose tissue injections, which are often marketed as “stem” cell injections and are currently available at orthopaedic clinics across the United States [27].

In the US, the rules governing the clinical use of treatments claiming to be “minimally manipulated”, particularly intra-articular adipose tissue injections, are ambiguous. This ambiguity can be attributed to special regulatory exemptions for blood-derived cell products [28], as well as Section 361 of the US Public Health Service Act, which exempts certain human cells, tissues, and cellular and tissue-based products (HCT/Ps) from the regulations that require regulatory submissions for the conduct of clinical trials and marketing [29]. Orthopaedic surgeons administering these treatments claim that they are being administered for reconstruction, repair, and replacement, and that the mechanical processing of the fat does not alter the original relevant characteristics of the transferred tissue [30]. Opponents argue that, despite the presence and importance of fat in the knee joint [31], subcutaneous fat is very different than the adipose tissue of the knee joint, and so the injection of adipose tissue into the intra-articular space should not be considered homologous use. Despite regulatory ambiguity and little evidence demonstrate their effectiveness [32], “minimally manipulated” adipose tissue injections are widely available at clinics throughout the US. To date, there have been no randomized, controlled clinical studies performed to evaluate the efficacy intra-articular adipose tissue injections for the treatment of OA.

### Basic science for clinical study aspects

The principle difference between cell therapies and “minimally manipulated” fat injections is that fat injections are not enzymatically digested. As a result, autologous fat treatments contain both autologous cells, including MSCs [33], and extra-cellular matrix (ECM). Therapies containing ECM are thought to have the following advantages over treatments prepared using enzymatic digestion: (1) preservation of the stromal vascular niche, which allows time-release of the regenerative factors [34]; (2) release of bioactive molecules by exosomes, which have been demonstrated to be significantly greater in mechanically processed fat than enzymatically processed fat [35]; and (3) maintenance of the structural and morphologic unit, which is thought to increase efficacy by making the cells more resilient to the harsh, inflamed conditions in the recipient environment [36]. Enzymatic digestion, which is used to remove the cells from ECM, may remove critical elements involved in tissue repair and may damage the cells, affecting their function and viability. In vitro studies have suggested that cell-containing lipoaspirate obtained without enzymatic digestion may act as a scaffold when administered via intra-articular injection, allowing for the formation of fibrous tissue that provides mechanical support [37]. While non-enzymatic processing produces a lower progenitor cell yield [38, 39], the preserved ECM and growth factors are thought to contribute to the treatments’ overall therapeutic effectiveness.

Preclinical [37] and clinical [40, 41] studies investigating the use of “minimally manipulated” adipose tissue injections have demonstrated preliminary safety, but a number of questions remain unanswered. While ECM has been shown to be beneficial for tissue repair [42] and is commonly used to as a bridging material between new and old tissues [43], these advantages are less applicable to intra-articular fat injections because there are no tissue fragments for the ECM to bridge [44] and because agents injected into the joint tend to be quickly cleared from the body [45]. Most importantly, ECM itself has the potential to produce inflammatory signals [46]. In fact, collagen fragments are known to induce arthritis in animals [47].

### Feasibility justification for clinical aspects of the study

Adipose tissue will be obtained and administered in a single point-of-care procedure. The rapid processing (approx. 20 min) within a closed system reduces the possibility of contamination. However, this also means that the specific composition of the adipose tissue therapy cannot be determined prior to injection. As a result, there will be inherent, unavoidable variability between the treatments that participants receive. In order to help minimize this variability, each patient will receive exactly 6 ml of processed adipose tissue. The decision to inject 6 ml is based on anatomic considerations and the principal investigator’s clinical experience. A 6 ml injection is conservative, as the synovial fluid volume has been estimated to be 6.7 +/− 2.3 ml [48], with the average volume of the knee joint itself being 131 ± 53 ml [49]. The 6 ml “dose” is also in line with published case studies, where fat processed with the Lipogems® device has been injected into the knee [40]. Lastly, a 6 ml volume improves comparability because the comparator treatment is also a 6 ml intra-articular injection.

The entire fat transfer procedure will be completed in under an hour. Adipose tissue will be harvested from the abdomen using lipoaspiration, which does not require general anesthesia [50]. The tissue will be mechanically broken down using the Lipogems® device. While a number of other similar fat processing systems are available [51], the differences between the products produced by different systems and their implications for osteoarthritis are unclear [32].

Our study will use Hyaluronic acid (HA) as an active control. In accordance with the requirements for the administrations for HA, only patients that fail to respond to the standard conservative treatment options (exercise, analgesics, NSAIDS [7]) will be recruited. The use of HA as an active control for autologous cell-based therapies is well-established [52, 53]. We have chosen to use Synvic One® because it has been included in more than 300 publications and has been used to treat more than 13 million knees worldwide. Synvic One® is also an ideal comparator treatment for this study because it has been shown to have an effect that last for up to 6 months [54].

### Study overview

This is a prospective, single-center, parallel-group, randomized, controlled study. The aim of this study is to estimate statistical power and gather preliminary efficacy data. Qualified participants will receive either a single, intra-articular injection of autologous adipose tissue or a single, intra-articular injection of HA. We hypothesize that participants treated with autologous adipose tissue will show a greater improvement in pain (as determined using the pain items of the Western Ontario and McMaster Universities Osteoarthritis Index, or WOMAC-A) than participants treated with HA. WOMAC (full questionnaire), the 29-point Patient-Reported Outcomes Measurement Information System (PROMIS®) profile, and clinical anchors will be used as secondary clinical outcome measures. Synovial fluid samples and excess adipose tissue (treatment group) will also be analyzed to gain a better understanding of how adipose tissue affects the biochemical environment of the joint.

## Methods

### Participants, interventions, and outcomes

All study-related activities will be performed at the USC Department of Orthopaedic Surgery Outpatient Clinic, including subject identification, screening, treatment, and outcome assessments. Patients between the ages of 45 and 75 with Kellgren-Lawrence grades 2–3 OA (inclusive) that are interested in participating in the study will be screened for eligibility by the principal investigator using pre-defined criteria (Fig. 1). Those who meet inclusion/exclusion criteria and decide to participate will sign an informed consent before randomization (see Assignment of Interventions). Because the fat treatment requires the removal of adipose tissue from the abdomen, participants will not be blinded to their assigned group.

**Fig. 1 Fig1:**
[figure not shown]
Study design flow chart

Male and/or female patients will be randomized to either the HA (Synvic One®) treatment group (*n* = 27) or autologous fat (Lipogems®) treatment group (n = 27). To ensure enrollment goals are met, the investigator will draw from a waitlist of current patients that have expressed interest in participating in clinical trials. We also have IRB-approved flyers/brochures that will be shared with patients and nearby orthopaedic clinics (Additional file 1). Additionally, to improve adherence to the intervention protocol, participant who are allocated to the control group that complete all scheduled follow-up visits will be offered the adipose tissue treatment at the end of their final visit at no cost.

Since our primary aim is to estimate the effect size for future well-powered studies, we estimate the precision around which we can measure the effect. Based on a prior study using similar methods, but comparing WOMAC-A scores among patients receiving placebo to Hylan G-F (a joint lubricant) [54], we assumed standard deviations in the control and treatment groups of 0.66 and 0.67, respectively. With a sample size of 54 (27 per group), we will be able to estimate a two-sided 95% confidence interval within ±0.36 distance from the mean difference. For our secondary aim, we estimated the mean difference we would be able to detect, assuming a similar effect size for HA as was observed for Hylan G-F (μ = − 0.84, σ = 0.67) and found that we would have 80% power to detect a mean difference of − 1.4 in the autologous adipose group with a two-sided Type I error rate of 0.05.

Power was calculated using Pass 14 (Kaysville, UT).

At the treatment visit (day 0), patients will be randomly assigned to receive either a single intra-articular, ultrasound-guided injection autologous adipose tissue (6 ml) or a single intra-articular, ultrasound-guided injection of hyaluronic acid (6 ml). Patients with bilateral OA will be allowed to participate in this study, but only their more painful eligible knee will be treated (as determined by WOMAC-A). To control for possible responder differences between bilateral and unilateral symptomatic patients [55, 56], WOMAC-A for the contralateral knee will be obtained at baseline, 6 weeks, and 6 months (Table 1). If a participant has bilateral OA of equal pain intensity in both knees, the treatment knee will be selected randomly.

**Table 1 Tab1:** Study Calendar

Timepoint**	Study period				
	Screening	Allocation	Follow-up visits		Close-out
	Day − 21 to 0	day 0	Safety follow-up visit Day 2–7 (inclusive)	Week 6 ± 7 days	Month 6 ± 30 days
Enrolment:					
Eligibility screen	X				
Informed consent	X				
*Focused physical exam*		X	X	X	X
Randomization / Allocation		X			
Interventions:					
*Autologous Adipose Tissue Injection*		X			
*Hyaluronic Acid Injection*		X			
Assessments:					
WOMAC	X	X		X	X
WOMAC-A (contralateral knee)	X	X		X	X
PROMIS-29		X		X	X
Force Plate Analysis (bilateral)		X		X	X
Clinical anchors		X		X	X
Synovial fluid aspiration		X		X	X

The *eligibility screen* includes a detailed physical exam/medical history and pregnancy testing (if applicable). The *focused physical exam* includes Height/weight/vitals, concomitant medications, knee exam, and wound evaluation (if applicable). Only patients that receive the fat treatment will be asked to come in for the safety follow-up. All assessments pertain only to the study knee, unless otherwise indicated

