### Data collection, management, and analysis

Demographics and survey data will be stored using a REDcap database created specifically for the purpose of this study. REDcap has several security features, including off-site backups, an audit trail, secure logins, de-identified data exports, and built-in filtering methods to ensure data quality. Additionally, survey answers (clinical outcome data) will be directly entered into the database by the participants via iPad before they interact with the examining physician. Documentation not included in the quantitative analysis of clinical outcomes will be recorded using traditional source documents (Additional files 2 and 3). These documents will be kept in the participant’s binder and locked in a secure location. All data collection will take place in the clinic.

Only those who require access to the database will be given access. Coding of the variables will be done within the database. A completed data file will be stored by the statistician in the shared folder for the Clinical Translational Science Institute Biostatistics core at USC and will be backed up regularly. The statistician’s access to the database will be limited to de-identified data. Data quality will be assured by range checks for unusual or impossible data values. Data management will include a thorough data cleaning (checking ranges, evaluating distributions) and deriving of variables needed for analysis.

All protocol deviations will be recorded. The same outcome data will be obtained from all participants, regardless of protocol adherence. In order to promote retention and compliance, participants that receive the HA treatment and complete all schedule follow-up visits will be offered the fat treatment at the 6-month (final) follow-up visit at no charge. Imputation will be used if loss to follow-up is uncommon.

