Preliminary analyses will include descriptive statistics of basic demographic and clinical characteristics to assess the degree to which randomization was effective in balancing treatment groups. If any factors are found to have clinically significant differences, they will be considered and evaluated as possible confounders. The analysis will be by intent-to-treat. That is, all subjects will be analyzed according to randomization status, regardless of actual treatment received, compliance with therapy, or adherence to the study protocol. We will compare the outcome, difference in WOMAC-A score from baseline to 6 months, between the treated and untreated groups using generalized linear models (GLM) with a Gaussian family specified, assuming the data are normally distributed. If the data are not normally distributed, we will specify a more appropriate distribution based on an evaluation of the data via histogram. We will also use GLM to examine the relationship between the treatment and outcome at each time point at which the WOMAC was measured. Last, we will model the effect across all time points using a multi-level mixed effects model to account for repeated measures. Confounders will be defined as those variables that were found to differ between groups either at baseline or post-randomization and which, when added to the model, alter the effect estimate by > 15%. Potential a priori confounders include BMI, Bilateral vs contralateral OA, gender, ethnicity, and race. Potential interactions between treatment and visit will be evaluated. A *p*-value of <.05 will be considered statistically significant. The 29-point PROMIS® questionnaire will be evaluated using GLM at each measured time point and across time points using a multi-level mixed effects model, as described above. Missing data, if ≤5%, will be imputed using multiple imputation methods. Any covariate missing > 5% will not be included in the analysis.

A per-protocol analysis will also be conducted including only those participants who were protocol-adherent. Protocol adherence is defined as: (1) Receiving the assigned study treatment and (2) completing all follow-up visits. Lastly, sensitivity analyses will be conducted to assess the impact of using multiple imputation methods, if such methods are employed in the analysis.

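### The only retention incentive described is for the HA arm, and outcomes are collected only in the clinic, so month-6 losses could depend on arm and response, with no route to recover the primary outcome

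*Protocol article*

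**What the plan says.** **The incentive.** In the Protocol article, Methods, Participants, interventions, and outcomes (text after Fig. 1), control participants "that complete all scheduled follow-up visits will be offered the adipose tissue treatment at the end of their final visit at no cost". Data collection, management, and analysis repeats the offer and gives retention and compliance as its purpose: "participants that receive the HA treatment and complete all schedule follow-up visits will be offered the fat treatment". The article describes no counterpart for the fat arm.

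**Blinding.** Participants, interventions, and outcomes states that "participants will not be blinded to their assigned group". Everyone therefore knows whether the offer applies to them.

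**Where outcomes are collected.** Data collection, management, and analysis states that "All data collection will take place in the clinic", and that "survey answers (clinical outcome data) will be directly entered into the database by the participants via iPad". No route is given for a person who does not attend. The same section states an aim: "The same outcome data will be obtained from all participants, regardless of protocol adherence".

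**What depends on it.** The main comparison is the "difference in WOMAC-A score from baseline to 6 months". Multiple imputation is planned only when no more than 5% of data are missing. The per-protocol set requires completion of all follow-up visits.

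**The concern.** Three stated features act together: a completion reward in one arm, knowledge of the assigned arm, and outcome collection tied to attendance. The free fat injection is likely to be worth most to an HA participant who is still in pain, so the offer could preferentially keep poor HA responders in the data. A fat participant still in pain has no comparable offer. If such participants stop attending, the retained fat arm looks better than the randomised fat arm, and the month-6 contrast moves towards fat.

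The stake is the trial's main product. The primary aim is to estimate an effect size for planning later, well-powered studies, so a bias from retention would carry into their sample sizes. The analysis can do little about it afterwards, because an outcome that was never collected cannot be restored.

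**Working it through.** **Inputs from the article** (Participants, interventions, and outcomes): 27 per group; assumed SDs 0.66 (control) and 0.67 (treatment); assumed mean change on HA −0.84; stated precision ±0.36. No dropout rate is given, overall or by arm, so every loss scenario below is an assumption.

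**1. The plan's own figure.**
SE = √(0.66²/27 + 0.67²/27) = √(0.8845/27) = 0.181.
Half-width = 1.96 × 0.181 = 0.355 (normal), or 0.363 with the t distribution on 52 degrees of freedom. The stated ±0.36 is reproduced. It uses all 27 per group, so it contains no allowance for loss.

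**2. Bias from selective loss in the fat arm.** Let *d* be the fraction lost and Δ the amount by which the mean change of those lost is worse than that of those retained. The full-arm mean is (1 − *d*) × retained mean + *d* × lost mean, so the retained mean is too favourable by *d* × Δ. With HA loss unrelated to response, this is also the bias in the difference.

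| Assumption | Bias towards fat | Share of 0.36 |
|---|---|---|
| 4 of 27 lost, Δ = 0.67 (one SD) | 4/27 × 0.67 = 0.099 | 28% |
| 5 of 27 lost, Δ = 0.84 | 5/27 × 0.84 = 0.156 | 43% |

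The value Δ = 0.84 means that those lost did not improve while those retained improved by 0.84. That borrows the HA mean for the fat arm, so it supposes no treatment difference.

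**3. A second method.** Outcomes were simulated as normal with SD 0.67 and no true difference, 40,000 trials per scenario, analysed by complete-case t-test. The correlation between dropping out and a poor outcome was set by assumption.

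| Lost (fat, HA) | Correlation | Bias towards fat | Significant result favouring fat |
|---|---|---|---|
| 0, 0 | – | about 0 | about 2.5% |
| 3, 0 | 0.5 to 1 | 0.07 to 0.14 | 6% to 13% |
| 5, 0 | 0.5 to 1 | 0.10 to 0.21 | 8% to 23% |
| 5, 1 | 0.5 to 1 | 0.08 to 0.16 | 6% to 18% |
| 5, 5 | 0.5 to 1 | about 0 | 3% to 5% |
| 5, 0 | 0 (loss unrelated to outcome) | about 0 | about 2.5% |
| 5, 0 | −0.5 (good responders lost) | −0.11 (against fat) | under 1% |

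The sign and size depend entirely on who is lost, and the article says nothing about that.

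**4. Whether the planned analysis would repair it.** The 5% limit on imputation is 0.05 × 54 = 2.7, so at most 2 missing outcomes. Losing 4 or 5 people is 7.4% or 9.3% of 54, above the limit. The mixed model across time points can use week-6 data, but only from people who attended week 6, and only if the loss is missing at random. The per-protocol set conditions on attendance and so contains the same selection.

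**The case against.** The strongest reply is that the offer may narrow a retention gap rather than open one. In an open-label trial, HA participants know that they did not get the new treatment and have their own reason to leave. Without the offer, HA retention might be the worse of the two. Nothing in the article shows that retention would be equal without it. This stands, and it is why the offer should be kept.

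A reader might infer that fat participants who do poorly *will* be missing more often, and that the result is therefore biased towards fat. The article does not support that. It gives no dropout pattern. The week-6 and month-6 aspirations are scheduled in both arms, so they are not in themselves a fat-arm deterrent. Each follow-up visit includes a knee examination, which may draw back someone still in pain. The extra fat-arm safety visit adds contact as well as burden.

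A reader might also infer that no other retention measure exists. Reminders, missed-visit contact or payments may sit in the full protocol or the consent form, which are not shown. Only the article's own description can be relied on.

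Nor is there a contradiction between clinic-only collection and the aim that "The same outcome data will be obtained from all participants, regardless of protocol adherence". Intent-to-treat and that aim are sound. They simply come with no stated means of reaching someone who does not attend.

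What survives is the affirmative rule that "All data collection will take place in the clinic". It is a stated rule and not a silence that a condensed article would explain, and it ties the primary outcome to attendance.

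**Conclusion.** The point holds as a design weakness and not as a demonstrated bias. An incentive described for one arm, unblinded participants and clinic-only collection mean that retention *could* depend on arm and response, and that a missed month-6 visit loses the primary outcome.

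Under the assumed losses (4 to 5 of 27 in the fat arm, 0.67 to 0.84 worse than those retained, HA loss unrelated to response) the bias is 0.10 to 0.16 towards fat, or 28% to 43% of the stated ±0.36. Under other assumptions that the article equally allows, it is about zero or runs against fat. The direction is possible and not established. The case for acting rests on how cheaply the exposure can be reduced and on the fact that uncollected outcomes cannot be recovered by analysis.

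**What to change.** In Data collection, management, and analysis, replace the sentence "All data collection will take place in the clinic" with text to this effect:

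> Outcomes are collected in the clinic by default. Any participant in either arm who misses the week-6 or month-6 visit is sent the same self-completed REDCap questionnaires (WOMAC, contralateral WOMAC-A, PROMIS-29 and clinical anchors) by secure link, for completion within the visit window (week 6 ± 7 days; month 6 ± 30 days). Completion and mode of completion are reported by arm.

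Keep the HA offer. Do not add interviewer-read telephone collection: direct self-entry before meeting the physician is the article's stated safeguard against investigator bias, and an interviewer would weaken it. A completion payment is not needed for this repair and is debatable, given that the Discussion says funding fixes the trial's size. Since the per-protocol set depends on completed visits, the text should also say how a remote questionnaire counts for that set.

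The cost is a change to protocol and consent wording and a REDCap survey link. The downside is a possible mode effect in a few remote questionnaires, which reporting by mode makes visible. Synovial fluid and force-plate data would still be lost for non-attenders, but the primary outcome would not have to be.

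### Control for bilateral disease is not assured: adjustment rests on a data-driven rule that names no use for the contralateral WOMAC-A score and could admit post-randomization values of it

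*Protocol article*

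**What the plan says.** **Design.** In Methods, under Participants, interventions, and outcomes, patients with bilateral OA may enter and only the more painful eligible knee is treated. The other knee is then scored for a stated reason: "To control for possible responder differences between bilateral and unilateral symptomatic patients", "WOMAC-A for the contralateral knee will be obtained at baseline, 6 weeks, and 6 months". Table 1 (Study Calendar) schedules this score at screening, day 0, week 6 and month 6.

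**Analysis.** Data collection, management, and analysis compares the change in study-knee WOMAC-A from baseline to 6 months between arms with a Gaussian GLM, then fits a GLM at each time point, then a mixed model over all visits. No covariate is fixed in advance in any of these. The candidates are given as: "Potential a priori confounders include BMI, Bilateral vs contralateral OA, gender, ethnicity, and race". A candidate counts as a confounder if it is among "those variables that were found to differ between groups either at baseline or post-randomization" and if adding it would "alter the effect estimate by > 15" per cent. The only interaction mentioned is this: "Potential interactions between treatment and visit will be evaluated".

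**The concern.** The design section gives the contralateral score one job, which is control for bilateral disease. The analysis section does not commit to that job. There are three gaps.

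- Whether bilateral status is adjusted for depends on two conditions that are read from the trial's own data.
- The score that was collected for the purpose appears in no named model and is not in the candidate list. Its link to the listed bilateral item is left undefined, and the wording of that item is not a usable contrast.
- The entry rule accepts variables that differ after randomization. The contralateral score is taken at week 6 and month 6, so those values could qualify. They are measured after an open-label treatment that may itself affect them, and adjusting for them could bias the treatment effect.

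The trial's primary aim is to estimate an effect size with stated precision. A change-in-estimate rule selects covariates by how far they move the estimate, not by how much outcome variance they explain. A prognostic covariate that happens to be balanced is left out and its precision is forgone. Whether the reported estimate is adjusted at all becomes a result of the data.

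**Working it through.** **1. The plan's own precision figure.** Inputs from the sample-size paragraph: 27 per arm, SDs 0.66 and 0.67, two-sided 95%.

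- SE = sqrt(0.66²/27 + 0.67²/27) = 0.1810
- Half-width = t(0.975, 52) × SE = 2.0067 × 0.1810 = 0.363

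The plan states ±0.36, so the figure reproduces. (With 1.96 in place of t it is 0.355.)

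**2. Effect of one fixed baseline covariate.** The share of residual variance it explains, R², is not in the document, so a range is assumed. Two costs are charged: one degree of freedom (52 to 51), and the usual variance inflation for one estimated covariate, about 1 + 1/(N − 4) = 1 + 1/50 with N = 54.

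Half-width = t(0.975, 51) × SE × sqrt(1.02 × (1 − R²)) = 2.0076 × 0.1810 × 1.00995 × sqrt(1 − R²) = 0.367 × sqrt(1 − R²)

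| Assumed R² | Half-width | Against 0.363 |
|---|---|---|
| 0 | 0.367 | wider by 0.004 |
| 5% | 0.358 | narrower by 0.005 |
| 10% | 0.348 | narrower by 0.015 |
| 20% | 0.328 | narrower by 0.035 |

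The break-even point is 1 − (0.363/0.367)², or about 2% of residual variance. At 5% the result still rounds to the plan's ±0.36.

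**3. How often the 15% condition alone would admit bilateral status.** This is an illustrative simulation with 5,000 trials per scenario, 27 per arm and residual SD 0.67. The outcome is the treatment difference plus a bilateral effect plus normal error. The estimate is computed with and without a binary bilateral indicator, and the relative change is compared with 15%. The difference of 0.56 is the gap between the plan's −0.84 and −1.4. The difference of 0.25, the prevalences and the bilateral effects are assumptions.

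| Bilateral prevalence | Bilateral effect | True difference 0.56 | True difference 0.25 |
|---|---|---|---|
| 30% | 0.33 | 12% | 37% |
| 30% | 0.67 | 32% | 61% |
| 50% | 0.33 | 14% | 41% |
| 50% | 0.67 | 35% | 64% |
| 70% | 0.33 | 12% | 38% |
| 70% | 0.67 | 31% | 61% |

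The range is about 12% to 64%. The further requirement that the variable differ between arms can only lower it. Entry is more common when the true difference is small, because 15% of a small estimate is easily exceeded. The rule therefore reacts to the size of the treatment effect as well as to bilateral disease.

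**4. The two sections side by side.**

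| Item | Design section | Analysis section |
|---|---|---|
| Purpose | control for bilateral versus unilateral differences | adjust only if both conditions are met |
| Variable | contralateral WOMAC-A score | bilateral status, worded as a contrast with contralateral OA |
| Timing | baseline, week 6, month 6 | baseline or post-randomization differences both admitted |

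**The case against.** A reader might infer that the score will not be used and the promised control is absent. The text does not support that. Bilateral status is a named candidate. The list is introduced as open, and the same section says that any factor with a clinically significant difference between arms will be evaluated as a possible confounder, so the score itself could qualify. The contralateral score may also be what defines whether the second knee is symptomatic. In step 3 the indicator enters in a sizeable share of simulated trials. Adjustment is uncertain, not ruled out.

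Other parts of the opposing case also stand:

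- The protocol speaks only of possible responder differences. It does not claim that bilateral disease is prognostic, and it gives no strength for it.
- How the score is turned into a covariate is ordinary analysis-plan detail, and a fuller plan may exist.
- In a randomized comparison the unadjusted estimate is unbiased, so leaving out a baseline covariate is not an error in itself.
- The odd label is a wording slip. No coding is shown, so no coding error can be claimed.
- Data-driven selection affects BMI, gender, ethnicity and race equally.

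These points do not dispose of the matter. The selection rule is written in the article, not deferred. It does not secure the control that the design section gives as the reason for collecting the score, and its wording opens the door to post-randomization values.

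**Conclusion.** The point holds in this form: control for bilateral disease is conditional and data-dependent, its link to the contralateral score is undefined, and the rule as worded could admit week-6 or month-6 contralateral scores as covariates.

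The precision at stake is unknown and probably modest. It runs from a loss of about 0.004 in half-width if the covariate explains nothing to a gain of about 0.035 if it explains 20% of residual variance. Those R² values are assumed, and nothing in the document shows that the baseline contralateral score predicts change in the treated knee. The entry frequencies in step 3 likewise rest on assumed prevalence and effects. The firmer argument is that a pre-specified model yields an estimate that does not hinge on chance imbalance or on a change-in-estimate threshold.

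If responder differences is meant as a different treatment effect in bilateral patients, a main-effect covariate does not test that, and the only interaction the plan names is treatment by visit.

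**What to change.** In Data collection, management, and analysis:

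1. Pre-specify one baseline covariate, either day-0 contralateral WOMAC-A or baseline bilateral versus unilateral status, in the primary 6-month GLM and in the mixed model, whatever the imbalance and without the 15% rule. If bilateral status is chosen, say how it is defined and whether the contralateral score defines it.
2. Correct the label to bilateral vs unilateral OA.
3. State that week-6 and month-6 contralateral scores are described by arm and not used for adjustment.
4. Say that the covariate adjusts for a main effect only and is not a test of effect modification.

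The cost is a few sentences and one degree of freedom. The score is already scheduled, so no new data are needed. If the covariate explains less than about 2% of residual variance, the interval becomes very slightly wider. The edit should be made before outcome data are examined by arm.
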